### 2.3. Discontinuation of Interventions

The investigator will terminate the study if any of the following conditions occur: the emergence of worsening complications; the development of a condition potentially linked to the research; pregnancy; an allergic reaction to the test drug; severe kidney or liver dysfunction; difficulty in continuing the medication; or if the participant is deemed ineligible to continue taking the drug for any other reasons.

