## 3. Procedure

### 3.1. Recruitment

Informed written consent will be obtained from all patients or their legal representatives before inclusion in the study, in line with institutional and national ethical guidelines. Participant will be made aware that their involvement is voluntary and that they can withdraw from the study at any time.

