### 3.3. Participant Timeline

The overall duration of the project is 16 months, with a screening period (4 months), an open-label treatment phase (6 months), and a follow-up period (6 months). Patients will undergo a clinical evaluation at baseline (week 1, before the administration of empagliflozin 10 mg/day), at the intermediate time point (three months), and at the end of treatment (six months). Sub-analyses will also compare seizure rates at intermediate time points. The progression of other LD symptoms will be evaluated at 6 months and compared to the baseline. Changes in FDG-PET and MRI findings will be categorized as stable, improved, or worsened.

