The following endpoints for the safety and efficacy of empagliflozin will be evaluated from baseline to month 6:Safety: Type, severity, incidence, and timing of adverse events; incidence of treatment discontinuation due to adverse events; and changes in vital signs, ECG, and laboratory parameters.Efficacy: Change in the frequency of generalized tonic–clonic seizures compared to the 6 months prior to the study; EEG: changes in posterior background activity and frequency of epileptiform abnormalities; cognitive function: changes (no worsening or improvement) in neuropsychological assessments; motor function: changes (no worsening or improvement) in motor function assessments; global function and autonomy: changes (no worsening or improvement) in LDS, LESS, ADL, IADL, Barthel Index, Vineland-II, and CGI-I and PGI-CaGI-C scales.Biomarkers: Brain FDG-PET: changes (no worsening) in areas of cerebral hypometabolism. High-field brain MRI (3 Tesla): changes (no worsening) in measures of cerebral atrophy. Direct measurement of CSF polyglucosan levels, although potentially informative, is not feasible within the constraints of this pilot study. Thus, brain FDG-PET imaging is included as a surrogate biomarker to assess changes in cerebral metabolism. This choice was primarily due to the significant logistical challenges associated with sample collection and processing for this ultra-rare disease, as well as to the absence of widely available, fully validated assays for the quantitative analysis of CSF polyglucosan levels.

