### 3.5. Ethics and Dissemination

#### 3.5.1. Ethics Approval and Consent to Participate

The study protocol has been approved by the Hospital Management Office of the Neurology Unit at IRCCS Casa Sollievo della Sofferenza Hospital, San Giovanni Rotondo (Foggia). Prior to inclusion in the study, written informed consent will be obtained from all patients, who will be informed that participation is completely voluntary and that they can withdraw from the study at any time.

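### Section 2.3 orders the study terminated for what are mostly reasons to stop the drug in one participant; followed literally, it ends observation at the stop

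*Protocol article*

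**What the plan says.** The heading of section 2.3 concerns discontinuing the intervention. Its single sentence gives one action, "The investigator will terminate the study if any of the following conditions occur", and then seven conditions. In paraphrase these are: worsening complications, a condition possibly connected with the research, pregnancy, allergy to the drug, serious renal or hepatic impairment, trouble continuing the medication, and, last, "if the participant is deemed ineligible to continue taking the drug for any other reasons".

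Elsewhere the article uses different words for stopping the drug and for leaving the study. Section 3.4 lists among the safety endpoints "incidence of treatment discontinuation due to adverse events". Section 3.1 tells participants that "they can withdraw from the study at any time", and section 3.5.1 repeats that "participation is completely voluntary and that they can withdraw from the study at any time".

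On timing, section 3.4 states that "endpoints for the safety and efficacy of empagliflozin will be evaluated from baseline to month 6". Section 3.3 schedules clinical evaluations at baseline, month 3 and month 6, and plans six months of treatment followed by six months of follow-up. Section 3.4 places MRI and FDG-PET at baseline, month 6 and month 12. Section 2.1 names safety and tolerability as the first objective, and section 2.4 sets the sample at two patients.

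No section says that a patient who stops empagliflozin early remains under observation.

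**The concern.** The heading and most of the conditions concern the drug, while the ordered action concerns the study. An investigator who applies the sentence as written would stop observing a patient at the moment the drug is stopped.

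Four of the seven conditions are safety events: worsening complications, a research-linked condition, allergy, and renal or hepatic impairment. For these, whether the event resolves or persists off drug is informative about its cause. In a study whose first objective is safety, that is a poor point at which to end observation. The stopped patient's remaining evaluations would go too. If the study itself is ended, so might those of a second patient who met no condition.

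**Working it through.** The article gives no figure for this rule, so there is none to reproduce. The check is a comparison of the text followed by a count.

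**Text**

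| Place | Subject | Word for the act |
|---|---|---|
| 2.3, heading | intervention | discontinuation |
| 2.3, action | study | termination |
| 2.3, last condition | one participant's dosing | ineligibility to continue |
| 3.4, safety endpoints | treatment | discontinuation |
| 3.1 and 3.5.1 | study, by the participant's choice | withdrawal |

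The heading and the last condition point to a drug stop in one person. The action does not. Nothing elsewhere settles which is meant.

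**Inputs for the count:** 2 patients (section 2.4); 2 post-baseline clinical evaluations each, at months 3 and 6 (section 3.3); 2 post-baseline imaging times each, at months 6 and 12 (section 3.4). Let *s* be the month at which one patient stops.

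**If observation ends for the stopped patient only**
- Planned post-baseline clinical evaluations: 2 × 2 = 4.
- Stop before month 3: 2 of 4 lost. Stop from month 3 to before month 6: 1 of 4 lost.
- Month-6 values: 2 − 1 = 1 of 2 remains in either case.
- Imaging: 2 × 2 = 4 post-baseline sessions planned; a stop before month 6 loses 2 of 4.

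**If the whole study ends**
- The other patient's month-6 value exists only if that patient started at least 6 − *s* months earlier.
- With simultaneous starts, any stop before month 6 leaves 0 of 2 month-6 values. With staggered starts, 1 of 2 may remain. The article does not give the interval between starts.

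**If only the drug is stopped and observation continues:** nothing is lost.

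**Chance that the rule is used.** The article gives no stop rate. For scale only, assume a per-patient probability *p*, independent between patients. The chance that at least one of two patients meets a condition is 1 − (1 − *p*)²:
- *p* = 5%: 1 − 0.95² = 9.75%
- *p* = 10%: 1 − 0.90² = 19%
- *p* = 20%: 1 − 0.80² = 36%

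These are illustrations, not estimates for this drug in this disease.

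**The case against.** The strongest reply is that this is loose drafting. The heading names the intervention, and pregnancy, allergy and trouble taking the medication are ordinary reasons to stop dosing in one person. The article is not careful with terms elsewhere either: section 2.2 calls the study controlled, whereas section 4 calls it single-arm without a control group. So the contrast in wording with sections 3.1, 3.4 and 3.5.1 is weak evidence of intent. This stands. The drug-only reading is plausible, and no passage states that observation ends.

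Second, most of the listed adverse-event endpoints would already be recorded. The type, severity and timing of the event, and the fact of discontinuation, are largely known by the time of the stop, and recovery off drug is not a listed endpoint. This also stands. The loss concerns later laboratory, ECG and vital-sign changes, later events, the course of the event off drug, and the month-6 efficacy and imaging values.

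Third, how visits continue after a stop is detail that an article may leave to the full protocol. That would answer a complaint about missing detail. It does not answer this one, because a rule is stated and its literal wording orders the wrong act.

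Fourth, a halt of the whole study after a suspected drug reaction could be a defensible precaution in two patients aged 10 to 22. This stands, and any corrected wording must keep the power to stop dosing in both.

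**Conclusion.** The wording should be corrected. Read literally, the rule would cost a stopped patient one or two of the two scheduled post-baseline clinical evaluations, the later imaging, and the off-drug course of the event. The study would keep 1 of 2 month-6 values. The other patient's remaining evaluations are at risk only if the whole study ends. All of this depends on a stop before month 6 and on the literal reading; otherwise nothing is lost.

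Three stronger readings are tempting, and the article does not support them:
- **That the authors intend observation to end.** The heading and the reference to one participant's dosing leave this open.
- **That all the time from the stop to month 12 is lost observation.** Section 3.3 names no clinic visit in the follow-up period, and section 3.4 places only imaging at month 12. The scheduled loss is the evaluations and imaging sessions counted above.
- **That the rule would selectively remove unfavourable results**, because worsening complications are a trigger and several endpoints are framed as absence of worsening. The article does not say that disease progression counts as such a complication.

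**What to change.** In section 2.3, replace the opening phrase with:

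> The investigator will stop empagliflozin in that participant if

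and add after the list:

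> A participant who stops the drug remains, if willing, in the scheduled month 3 and month 6 evaluations. Adverse events are followed off drug. Scheduled imaging is omitted only where the stop reason rules it out. Month-6 values are reported with on-drug or off-drug status. After an event potentially related to the drug, the investigator may also suspend or stop dosing in the other participant, whose observation continues.

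The seven conditions stay as they are. The last sentence keeps a precautionary halt of dosing in both patients within the protocol text itself, and separates that halt from ending data collection.

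The cost is small. The month 3 and month 6 evaluations are already scheduled. Following an adverse event off drug may need a contact that the article does not now name. The stopped patient carries the burden of the remaining visits and may decline them, as the consent provisions in sections 3.1 and 3.5.1 allow.

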### 2.4. Sample Size

This pilot study aims to evaluate the safety and efficacy of empagliflozin initially in two patients with genetically diagnosed LD in the early/intermediate stage of disease. The sample size of two patients was chosen based on the feasibility of recruiting patients with these specific characteristics and the exploratory nature of this pilot study.

### 2.5. Data Collection and Management

Data will be entered into an electronic database. The following baseline data will be collected: informed consent; inclusion/exclusion criteria; demographic data; comprehensive medical and neurological history; detailed history of epileptic seizures, including frequency of generalized tonic–clonic seizures in the last six months (based on previous clinical documentation and/or a seizure diary); and medication history.

All information of the study protocol and the results obtained will be collected by the investigator during the study period and stored at IRCCS Casa Sollievo della Sofferenza Hospital in San Giovanni Rotondo (Foggia, Italy).

### 2.6. Statistical Methods

Descriptive statistics will be used to summarize the data. For continuous variables, measures such as mean, standard deviation, minimum, maximum, and 95% confidence intervals will be calculated. For categorical variables, the frequency and percentage will be reported. Changes from the baseline to follow-up time points will be assessed.

The in silico and in vitro studies proposed here are complementary and will be conducted in parallel with the in vivo human study. The aim of these studies is to gain insight into the additional mechanisms of action of empagliflozin that may be relevant for LD.

### 2.7. In Silico Studies on Target Candidates

Molecular docking calculations will be performed to assess whether empagliflozin can interact with additional targets involved in glucose metabolism and relevant for LD, such as glycogen synthase (hGYS1) and glucose transporters (GLUT1 and GLUT3 isoforms), using Grid-based Ligand Docking with Energetics (GLIDE). To explore differences within the gliflozin class, parallel studies will also be conducted with dapagliflozin and canagliflozin. For each gliflozin, the docking score and ligand efficiency values will be calculated and compared to the respective reference ligand, taken as a positive control of each target protein considered.

As additional investigations, queries in a drug discovery web platform developed by some of us, namely PLATO (the acronym stands for Polypharmacology pLATform prediction), which allows the reverse ligand-based screening of small molecules [34] to be carried out, may allow further investigation into the putative gliflozins’ protein targets that are possibly involved in LB formation and neurodegeneration. Among the priority targets of gliflozins identified by PLATO, there is glycogen phosphorylase (GP), which is implicated in the formation of Lafora bodies and subsequent neurodegeneration.

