### 3.6. In Silico Screening

In silico screening will be performed using molecular docking calculations and reverse ligand-based screening.

For molecular docking calculations, the 3D structures of the targets and SGLT2 inhibitors will be optimized. Specifically, the X-ray structures of hGYS1 and hGLUT1/3 deposited in the Protein Data Bank with PDB codes 7Q13, 5EQG, and 4ZWC, respectively, will be used. Notably, the crystal structure of hGLUT1 presents an inward-open conformation, while that of hGLUT3 presents an outward-open conformation. A homology model will be built from the amino acid sequence (FASTA sequence) of hGLUT1, using the outward-open 3D structure of hGLUT3 (PDB: 4ZWC) as it shares 66% sequence identity. The Schrödinger Suite 2023-4 will be used to generate the structural model using the Prime software. All target structures will then be optimized using the protein preparation wizard (Schrödinger Suite 2023-4) to correct bond orders and add hydrogen atoms and any missing amino acid side chains and cycles. The 3D conformation of empagliflozin and other SGLT2 inhibitors will be processed using LigPrep to generate all possible tautomers and ionization states at a physiological pH of 7.4. Docking simulations will then be performed using Ligand Docking with Energetics (GLIDE) [44,45], which is part of the Schrödinger Suite. Specifically, docking simulations will be performed using the virtual screening workflow implemented in the Schrödinger Suite to consider both open conformations of the GLUT1/3 transporters. For each gliflozin, the docking score and ligand efficiency will be determined relative to the reference ligand for the target considered. To prove the reliability of the docking protocol, redocking simulations will be performed. By redocking the co-crystallized ligands into their respective binding sites and comparing the predicted poses with the experimental ones, using the RMSD (Root Mean Square Deviation) values, the docking methodology will be calibrated, ensuring its accuracy before proceeding with docking calculations with empagliflozin.

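### Docking scores are judged against a positive-control ligand only, so a gliflozin score near the reference cannot be told from background

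*Protocol article*

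**What the plan says.** Section 2.7 gives docking a yes-or-no purpose: "Molecular docking calculations will be performed to assess whether empagliflozin can interact with additional targets involved in glucose metabolism". The named targets are hGYS1, GLUT1 and GLUT3, and "parallel studies will also be conducted with dapagliflozin and canagliflozin".

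The yardstick is stated twice. In Section 2.7, "the docking score and ligand efficiency values will be calculated and compared to the respective reference ligand, taken as a positive control". Section 3.6 repeats it: "For each gliflozin, the docking score and ligand efficiency will be determined relative to the reference ligand for the target considered". Neither section names an inactive compound, a decoy set or a score cut-off, or says which of the two metrics decides.

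Section 3.6 adds one reliability check, redocking judged by RMSD: "By redocking the co-crystallized ligands into their respective binding sites and comparing the predicted poses with the experimental ones". It presents this as the calibration that secures accuracy before empagliflozin is docked. Section 2.8 then says that cell-line work will validate the predictions. Sections 2.8 and 3.7 give the readouts: glucose and glycogen levels in SH-SY5Y and HEK293 cells, with cytotoxicity in parallel.

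**The concern.** A docking program returns a score for any ligand that fits the site. A positive control shows what a known binder scores. It does not show what an unrelated molecule of similar size and polarity would score in the same site. Without that second reference, a gliflozin scoring close to the positive control may be a real ligand, or may score as many drug-like molecules would.

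Objective 2 (Section 2.1) is meant to uncover new mechanisms and strengthen the case for repurposing, and Section 4 expects these findings to guide later research. A target named on this evidence could direct further laboratory work with no estimate of how often a non-binder would have been named too.

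**Working it through.** The article states no docking threshold, error rate or hit rate, so there is no figure of its own to reproduce. The check has four parts.

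**1. What each planned element can show**

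| Element | Section | Shows | Does not show |
|---|---|---|---|
| Reference ligand | 2.7, 3.6 | Score of a known binder | Score of a non-binder |
| Redocking, RMSD | 3.6 | Known poses are reproduced | Binders outscore non-binders |
| Glucose and glycogen assays | 2.8, 3.7 | A change in level in cells | Which protein caused it |

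Two details sharpen this. The outward-open GLUT1 structure is a homology model built on GLUT3, so it has no co-crystallized pose of its own to redock. Section 3.2 also argues that SGLT2 inhibition may itself lower the glucose load, so a fall in intracellular glucose would not point to GLUT1, GLUT3 or hGYS1.

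**2. Two metrics, none deciding**

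Ligand efficiency is the score divided by molecular size, so it can rank two ligands in the opposite order to the score. With assumed values, a 12-atom reference scoring −6 has efficiency 6/12 = 0.50, and a 30-atom ligand scoring −9 has 9/30 = 0.30. The larger ligand wins on score and loses on efficiency.

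**3. Chance of at least one false hit**

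- Ligands: 3 (empagliflozin, dapagliflozin, canagliflozin; Section 2.7).
- Structures described in Section 3.6: 4 (hGYS1, inward-open GLUT1, outward-open GLUT1 model, outward-open GLUT3).
- Pairs: m = 3 × 4 = 12. The two metrics come from the same docked ligand and are not counted twice.
- q: the probability that a non-binder meets whatever criterion is applied. **Assumed**; not in the article.
- Formula, treating pairs as independent: P = 1 − (1 − q)^m.

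| q | m = 12 | m = 4 (three gliflozins acting as one ligand, or empagliflozin alone) |
|---|---|---|
| 1% | 1 − 0.99^12 = 11.4% | 3.9% |
| 5% | 1 − 0.95^12 = 46.0% | 18.5% |
| 10% | 1 − 0.90^12 = 71.8% | 34.4% |

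P exceeds 50% only if q is above 1 − 0.5^(1/12) = 5.6% for m = 12, or 1 − 0.5^(1/4) = 15.9% for m = 4. Section 3.6 says the workflow is meant "to consider both open conformations of the GLUT1/3 transporters". If that also implies an inward-open GLUT3 model, m rises to 15 and P becomes 14.0%, 53.7% and 79.4%.

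**4. What a decoy set would add**

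With N decoys per target, the empirical rank of a gliflozin is (1 + number of decoys scoring at least as well)/(N + 1), so its smallest value is 1/(N + 1). That is 0.05 for N = 19, 0.020 for N = 50 and 0.01 for N = 99. With no decoys, no rank exists.

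An unadjusted 95th-percentile rule sets q at about 5%, so the m = 12 and m = 4 rows above apply: 46% and 18.5%. To share 5% over 4 comparisons, each needs 0.05/4 = 0.0125, so N of at least 79 (1/80 = 0.0125). Over 12 comparisons, each needs 0.05/12 = 0.0042, so N of at least 239 (1/240 = 0.0042).

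**The case against.** **A journal article condenses, and decoys or cut-offs may stand in a fuller methods document.** This stands in part, and it limits confidence. But Section 3.6 is not sketchy: it gives structure codes, software version, preparation pH, homology template and the reliability check. It states which comparator is used and which check secures accuracy. The point is that the stated comparator is one-sided and the stated check answers a different question. It is not that the fuller plan is known to lack a negative reference.

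**The work is exploratory and has safeguards.** This stands as to consequence. Section 2.6 describes the in silico and in vitro studies as complementary and run in parallel, and nothing makes treatment or patient endpoints depend on a docking result. Redocking and the cell assays are real checks, but neither closes this gap.

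**A reader might infer that some interaction is likely to emerge by chance.** The documents do not support that. It depends wholly on q, which they do not give, and the table above runs from about 4% to 72%. If the working criterion were to match or beat a co-crystallized ligand, q could be low. Counting docking score and ligand efficiency as separate chances would inflate the figure further, since they are two readings of one docked ligand. Related gliflozins are not independent either.

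**A reader might also infer that the docking conclusion will be favourable whether or not the drug binds.** That goes too far. A score well below the positive control would count against a target under the comparison as written. The ambiguity lies with scores near the reference.

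**Conclusion.** The point holds as a limitation of the docking step's design. Sections 2.7 and 3.6 pose a yes-or-no question about interaction and answer it against one known binder per target. Nothing else described in the article tests whether binders score better than non-binders, or shows engagement of a named target. A score near the reference is therefore uninterpretable as evidence of binding.

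The size of the problem cannot be fixed from the documents. The conditional figures (11%, 46% and 72% at q = 1%, 5% and 10% over 12 pairs) assume both q and independence, and correlation between similar gliflozins or structures would lower them. The effect is confined to what exploratory Objective 2 can conclude. Safety, efficacy and biomarker endpoints in the patients are not touched. The change is worth making because it is cheap and lets the step answer its own question.

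**What to change.** In Sections 2.7 and 3.6:

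- Dock a set of property-matched decoys or known inactives for each target through the same workflow. For the glucose transporters, exclude compounds that are likely to be true ligands, such as close sugar analogues, since they would be a poor null.
- Name docking score as the deciding metric and keep ligand efficiency as descriptive.
- Report each gliflozin's rank among the decoys beside the comparison with the reference ligand.
- Make empagliflozin the primary ligand, with dapagliflozin and canagliflozin as class comparisons.
- Treat the rank as exploratory, and either state the number of comparisons or set a cut-off that allows for it. The decoy number should be large enough to resolve that cut-off: at least 79 per target for 5% shared over empagliflozin's four structures.
- Say that the glucose and glycogen assays test a cellular effect and do not confirm engagement of a docked target.

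The cost is a little extra computing on software already in use, with no patient involvement. The downside is that fewer predicted targets may survive.
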